### Statistical power and sample size

Calculations were made in consultation with a professional statistician. The sample size was calculated using NCSS (PASS 2002) programme, using data for hot flush frequency from many previous trials of HRT, herbs and acupuncture. With a baseline daily flush rate of 7.0 (SD 3.0), and assuming that the difference of interest is 20 percentage points (post-treatment flush rates of 3.5 and 4.9 for acupuncture and no acupuncture groups respectively, equivalent to reductions of 50% and 30%, and SD 3.5 for change in flush rate), and employing a two-sided, two-sample t-test for the changes, 100 women in each group were needed to identify a 20% difference with a power of 80% and α-value of 0.05. Assuming a total withdrawal and dropout rate of 30%, we estimated that a total sample size of 286 women is required.

Power calculations for the sub-study of biological variables are based on earlier studies of the CGRP excretion in urine during acupuncture treatment [15]. To identify a supposed 30% difference in CGRP urine excretion with a power of 80% and α-value of 0.05, we need 25–30 participants in each group. To allow for some measurement inaccuracies because CGRP and NYP are to be measured in early morning and evening urine samples, we will use 35 participants in each group.

Data entry is undertaken by the central coordinator, with checking of random 10% samples by the research fellow. Data on primary endpoint are entered by a person not connected to the study team, and who is blinded to treatment allocation.

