**Methods/Design:**

The study is a multi-centre pragmatic randomised controlled trial with two parallel arms. Participants are postmenopausal women who document ≥7 flushes/24 hours and who are not using hormone replacement therapy or other medication that may influence flushes. According to power calculations 200 women are needed to detect a 50% reduction in flushes, and altogether 286 women will be recruited to allow for a 30% dropout rate.

The treatment group receives 10 sessions of Traditional Chinese Medicine acupuncture-care and self-care; the control group will engage in self-care only. A team of experienced Traditional Chinese Medicine acupuncturists give acupuncture treatments.

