### Effect measures

Primary endpoint is mean number of hot flushes per 24 hours measured over a one-week period. The numbers of hot flushes are recorded in a daily diary, and flushes are scored by severity on a scale from of zero to ten. The diary is administered for two weeks during the qualifying period, and for one week after 4, 8 and 12 weeks of the intervention period.

Secondary endpoint is the Women's Health Questionnaire (WHQ), a validated, self-administered instrument containing 36 questions assessing a wide range of physical and emotional symptoms of women in the postmenopausal period [32]. A Norwegian version is available and has been validated linguistically. A psychometric validation of the WHQ will be performed during the study period. The WHQ is administered at baseline and at 12 weeks.

Baseline assessment includes sociodemographic data collected in a manner parallel to the NOWAC study [33], medical and gynaecological history, previous experience with acupuncture, which other self-provided and therapist-provided interventions they have used earlier to relieve their climacteric complaints, current use of drugs and dietary supplements, level of physical activity, smoking status and level of alcohol consumption.

At the end of interventions, all participants are asked which other self-provided and therapist-provided interventions they have used to relieve their climacteric complaints during the intervention period.

A hot flush diary and the WHQ are administered to participants in the acupuncture group at 6 and 12 months after the baseline evaluation. The follow up-period allows us to investigate the development of symptoms and the use of symptom relieving interventions after the intervention period (natural course of symptoms and choice of treatment).

At each treatment session the acupuncturists ask specifically about, and record, any adverse events that have occurred during or after the last treatment, and adverse event forms are filled in at 4, 8 and 12 weeks. The women are asked specifically about adverse events in the 8- and 12-weekly diaries.

The excretion of CGRP and NPY in early morning and evening urine samples are measured with a radioimmunoassay method [15], to determine any changes during the intervention period. The measurements are related to serum creatinine.

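### The sample size uses the entry minimum of 7 flushes/day as the baseline mean, so 3.5 v 4.9 and the equation of 20 percentage points with 1.4 flushes/day do not fit the eligible women

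*Protocol article*

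**What the plan says.** The abstract of the protocol article (Methods/Design) gives the entry rule: "Participants are postmenopausal women who document ≥7 flushes/24 hours". The full eligibility criteria are in table 1, which is not in the text available.

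Under Effect measures, only one diary precedes treatment: "The diary is administered for two weeks during the qualifying period, and for one week after 4, 8 and 12 weeks of the intervention period". The endpoint there is "Primary endpoint is mean number of hot flushes per 24 hours measured over a one-week period". So the baseline comes from the same record as the entry decision.

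Statistical power and sample size sets the planning inputs: "With a baseline daily flush rate of 7.0 (SD 3.0), and assuming that the difference of interest is 20 percentage points". The section then spells the target out as "post-treatment flush rates of 3.5 and 4.9 for acupuncture and no acupuncture groups respectively, equivalent to reductions of 50% and 30" per cent. It adds a change SD of 3.5 and a two-sided two-sample t-test on the changes, and arrives at 100 women per group for 80% power at α 0.05, or 286 in total after 30% dropout. The inputs are said to come from previous trials of HRT, herbs and acupuncture.

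**The concern.** The planning mean equals the entry minimum. If no enrolled woman can lie below 7, the group mean is 7.0 only when every woman has exactly 7, and then the baseline SD is 0, not 3.0.

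The mean has one job in the calculation: it converts the relative target (50% v 30%) into the absolute difference that the t-test uses (1.4 flushes/day). That conversion matters because the protocol works on two scales. The Background section judges clinical relevance as a relative reduction (50% or more), while Data analysis and handling compares mean changes in flush counts. If the enrolled mean is above 7, the two versions of the target separate. An observed difference of 1.4 flushes/day would meet the absolute target and miss the 20-point one. A reader using the sample size paragraph to interpret the result would not know which was intended, or what power the trial had for the relative one.

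**Working it through.** **1. The stated figures.** Inputs from the sample size section: difference 4.9 − 3.5 = 1.4 flushes/day; change SD 3.5; two-sided α 0.05; power 80%; equal groups.

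- Standardised difference: 1.4 / 3.5 = 0.40.
- Exact two-sample t-test: 99.1 per arm, stated as 100. Power at 100 per arm: 80.4%.
- Dropout: 200 / (1 − 0.30) = 285.7, so 286.

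All reproduce. The baseline SD of 3.0 does not enter. The baseline mean enters only through 0.20 × 7.0 = 1.4.

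**2. Baseline against the entry rule.** If every baseline value is at least 7 and the mean is 7.0, every deviation from the mean is non-negative and they sum to zero. All are then zero, and the SD is 0. Conversely, with a mean of 7.0 and an SD of 3.0, the share of women below 7 is 50% (normal) or 58% (log-normal).

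**3. How far the mean could move (assumption).** The documents give no mean for women at or above 7. As an illustration, let 7.0 (SD 3.0) describe women before selection, and cut at 7:

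- Normal: mean = 7 + 3 × √(2/π) = 9.39, SD 1.81.
- Log-normal with the same mean and SD: mean 9.72, SD 2.61. Data analysis and handling expects some right skew.

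**4. The two targets at other baselines.** 20 points = 0.20 × mean; 1.4 flushes/day in points = 140 / mean.

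| Enrolled mean | 50% v 30% reduction leaves | 20 points, flushes/day | 1.4 flushes/day, points |
|---|---|---|---|
| 7.0 (plan) | 3.5 v 4.9 | 1.40 | 20.0 |
| 8.0 | 4.0 v 5.6 | 1.60 | 17.5 |
| 9.4 | 4.7 v 6.6 | 1.88 | 14.9 |
| 9.7 | 4.9 v 6.8 | 1.94 | 14.4 |
| 12.0 | 6.0 v 8.4 | 2.40 | 11.7 |

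**5. Power for 20 points, 100 per arm, means 9.4 and 9.7.**

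| Change SD | Power for 20 points |
|---|---|
| Stays 3.5 | 96.6% and 97.4% |
| Scales with the mean at the plan's own ratio, 3.5 / 7.0 = 0.5 (4.70 and 4.85) | 80.4% at both |
| 6.0, i.e. grows faster than the mean | 60% and 62% |

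The last row is an arbitrary value, shown only to mark the direction.

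**6. Power for 1.4 flushes/day, 100 per arm.** This depends on the change SD alone, at any baseline: 80% at 3.5, 59% at 4.5, 50% at 5.0.

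**The case against.** **The arithmetic is right, and the power is not shown to fail.** This stands. The test uses only 1.4 and 3.5, and 80% is correct for that pair at any baseline. A reader might infer that the trial is underpowered. The documents do not support that: step 5 moves in both directions, and no change SD is given for women at or above 7.

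**Selection could even reduce the change SD.** Also fair. In a bivariate normal model with baseline 7.0 (SD 3.0), an unselected change SD of 3.5 and an assumed post-treatment SD of 2.0 to 3.5, cutting the baseline at 7 gives a change SD of 2.6 to 3.3. Power is then 85% to 96% for 1.4 flushes/day and 98% or more for 20 points. A larger SD needs a roughly proportional model, which the expected right skew makes possible but does not establish.

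**A baseline mean of 7.0 may not be strictly impossible.** A reader might infer flat impossibility. That holds only if the rule applies to the averaged qualifying diary. The abstract and Effect measures point that way, but table 1 is not shown. A rule applied to single days, or to another window, would let some averages fall below 7. Even so, a mean exactly on the threshold with an SD of 3.0 would need about half the women or more to average below it, which is implausible.

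**The inputs come from earlier trials, whose participants were probably selected too.** This stands as a limit on step 3. Reading 7.0 (SD 3.0) as women before selection is an assumption, so 9.4 to 9.7 is an illustration, not a forecast.

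**The tested scale is absolute, so the trial was plainly powered for 1.4 flushes/day at SD 3.5.** True. But the section names the difference of interest in percentage points first and treats the two as the same quantity.

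**Conclusion.** The concern holds as an inconsistency in the planning assumptions. The baseline input sits on the entry floor, so the expected rates of 3.5 v 4.9, and the equation of 20 percentage points with 1.4 flushes/day, do not describe the eligible women. That conclusion rests on the entry rule applying to the averaged diary; under a day-based rule it weakens from contradiction to strong implausibility.

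The size of the gap depends on an enrolled mean that the documents do not give. At 8 the absolute target is worth 17.5 points, at 9.4 to 9.7 it is worth 14 to 15, and at 12 it is worth 11.7.

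The sample size stands for 1.4 flushes/day with a change SD of 3.5. For 20 points in eligible women, 80% is unsupported: the true figure may be higher, equal or lower, depending on a change SD that is not stated for them. The point should be corrected, but it does not undermine the primary comparison.

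**What to change.** In Statistical power and sample size:

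1. Replace 7.0 (SD 3.0) with the baseline mean and SD, and the change SD, expected in women who meet the entry rule. Sources could be earlier trials with the same rule or, for the baseline figures, the qualifying diaries pooled without regard to allocation. State how the rule is applied to the diary.
2. Name one target scale and give its equivalent on the other at the new mean. Drop 3.5 and 4.9 as this trial's expected rates.
3. Restate power, or the detectable difference, for the fixed 200 evaluable (286 randomised) over a range of change SDs. With 100 per arm, the difference detectable at 80% power is 0.398 × SD: 1.39 flushes/day at SD 3.5, 1.79 at 4.5 and 1.99 at 5.0. Divide by the new mean to obtain percentage points.

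The cost is one recalculation and a few sentences. No women or procedures are added and recruitment does not change. The only downside is that the restated power or detectable difference may be less favourable.

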### Data analysis and handling

All analyses are conducted blinded to group allocation. Missing data are substituted by last value carried forward. The primary analysis is intention-to-treat, comparing mean changes from baseline to end of treatment after 12 weeks in the two groups, using a two-sample t-test. In the presence of meaningful baseline differences, analysis of covariance will be employed. It is anticipated that the data will be somewhat right-skewed, therefore analyses will be checked after appropriate data conversion, and also checked using non-parametric methods. Secondary analyses will compare the changes at different time points. Secondary measures will be analysed using appropriate parametric or non-parametric methods. Subgroup analyses include per-protocol analyses to assess efficacy of acupuncture care, and comparison of changes in hot flush rate among women grouped by TCM syndromes.

The trial headquarters is located at UNN Clinical Research Centre where they have experience in running multicenter studies. All data sheets are rendered anonymous by removing participant names and addresses. The personal information and the index that links trial numbers with individual participants is kept under lock and key in the possession of each local coordinator. Trial number alone identifies all computerised data. To prevent reporting bias, all the participant evaluation forms are administered by the trial headquarters in Tromsø. The participants return the evaluation forms to the trial headquarters in Tromsø.

Participants in either study group who choose to use any therapist-provided care to relieve hot flushes (e.g. massage, homeopathy or any prescribed medication to relieve hot flushes such as systemic estrogen or SSRI's from any source) during the 12 week study period, are followed up with registration of events and included in the intention-to-treat analysis.

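### Last value carried forward is the only stated missing-data rule for the primary analysis; it shrinks the estimate under equal dropout and biases it either way if dropout differs by arm

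*Protocol article*

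**What the plan says.** All locations are in the protocol article.

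- **Data analysis and handling:** the primary analysis is intention-to-treat, a two-sample t-test on mean change from baseline to 12 weeks. The missing-data rule is "Missing data are substituted by last value carried forward". The checks named alongside it (transformation, non-parametric methods) are there because skewed data are expected. They do not address missing values.
- **Statistical power and sample size:** the test is "employing a two-sided, two-sample t-test for the changes", with "post-treatment flush rates of 3.5 and 4.9 for acupuncture and no acupuncture groups respectively" and "SD 3.5 for change in flush rate". The result is that "100 women in each group were needed to identify a 20% difference with a power of 80% and α-value of 0.05". Then: "Assuming a total withdrawal and dropout rate of 30%, we estimated that a total sample size of 286 women is required".
- **Effect measures:** the diary is kept for two weeks before entry "and for one week after 4, 8 and 12 weeks of the intervention period". The value carried forward may therefore be baseline, week 4 or week 8.

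**The concern.** Carrying a value forward assumes no further change after the last diary. The plan's own figures assume the opposite: from a baseline of 7.0, flushes fall by 3.5 per day with acupuncture and by 2.1 without. A woman lost early is therefore held at a count higher than the one she would be expected to reach, and the t-test treats that value as observed.

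Two consequences follow.

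- If the arms lose equal shares at similar times, the difference between them shrinks.
- If they lose different shares, or lose women at different times, that imbalance itself becomes a difference in mean change, even when acupuncture adds nothing. The comparison is open: one arm receives up to 10 sessions and the other has self-care with a leaflet, so unequal dropout is plausible.

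The direction is not predictable. More dropout among controls favours acupuncture; more dropout in the acupuncture arm hides a real benefit. The rule cannot be defended as conservative.

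**Working it through.** **1. The plan's own figures.** Difference 3.5 − 2.1 = 1.4; SD of change 3.5; two-sided α 0.05; power 80%. The normal formula gives n = 2 × (1.96 + 0.84)² × 3.5² / 1.4², which rounds up to 99 per arm; the t-based value is 99.1, hence 100. Power at 100 per arm is about 80%. Inflation: 200 / 0.7 = 285.7, hence 286, or 143 per arm. The stated figures reproduce.

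**2. Assumptions not in the document.** These are the timing of dropout, its split between arms, and that women who leave would have changed like those who stay. Dropout is taken as monotone. All 143 per arm are analysed. A carried baseline gives a change of exactly zero; any other value has SD 3.5.

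**3. All dropouts lost before week 4.** For dropout share p and mean fall m:

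- mean = (1 − p)m
- variance = (1 − p) × 3.5² + p(1 − p)m²

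Equal 30%:

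- means 2.45 and 1.47, difference 0.98
- variances 11.15 and 9.50, SE = √(20.65 / 143) = 0.380
- z = 2.58, power 73%

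**4. Losses spread evenly: one third of dropouts before each of weeks 4, 8 and 12.** If a fraction a of the fall is reached by week 4 and b by week 8:

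- mean = m[(1 − p) + (p/3)(a + b)]
- variance = (1 − p/3) × 3.5² + m²[(1 − p) + (p/3)(a² + b²)] − mean²

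For a linear fall (a = 1/3, b = 2/3) at equal 30%:

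- means 2.80 and 1.68, difference 1.12
- variances 12.44 and 11.53, SE = √(23.98 / 143) = 0.409
- z = 2.74, power 78%

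| Pattern, equal 30% dropout | Expected difference | Power |
|---|---|---|
| All lost before week 4 | 0.98 | 73% |
| Spread, linear fall | 1.12 | 78% |
| Spread, 60% of fall by week 4, 85% by week 8 | 1.18 | 83% |
| Spread, 80% by week 4, 100% by week 8 | 1.23 | 86% |

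With all 286 values observed, power would be 92%.

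**5. No true effect (both arms fall 2.1), unequal dropout, acupuncture versus control.** With all lost before week 4 and a 20/40 split, the means are 0.8 × 2.1 = 1.68 and 0.6 × 2.1 = 1.26. The false difference is 0.42, with SE 0.364.

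| Pattern | 20% vs 40%: false difference, type I error | 25% vs 35%: false difference, type I error |
|---|---|---|
| All lost before week 4 | 0.42, 21% | 0.21, 9% |
| Spread, linear | 0.28, 11% | 0.14, 6.4% |
| Spread, 60%/85% | 0.22, 8% | 0.11, 5.9% |
| Spread, 80%/100% | 0.17, 7% | 0.08, 5.5% |

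**6. True difference 1.4, all lost before week 4.**

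- 40% acupuncture, 20% control: 0.6 × 3.5 − 0.8 × 2.1 = 0.42, power about 20%. With spread losses and a linear fall the difference is 0.75.
- 20% acupuncture, 40% control: 0.8 × 3.5 − 0.6 × 2.1 = 1.54, which is above the true value.

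**The case against.** **Power.** A reader might infer that the trial is underpowered, or that 286 was wrongly derived because the inflation treats dropouts as lost while the analysis keeps them. The document does not support either reading. The arithmetic is right, and analysing 286 women instead of 200 offsets much of the dilution. With spread losses, power is near or above 80%.

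**Worst case.** A reader might also take the 0.98 and the 21% as the expected outcome. Both require that no dropout has any diary after baseline, yet diaries are scheduled at weeks 4 and 8. They are the unfavourable end of the range.

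**Dropout figures.** The 30% is a planning allowance for withdrawal and dropout, not a forecast of imputed week-12 values. Women who turn to other therapist-provided care are followed up and kept in the intention-to-treat analysis, so that choice alone need not create missing data. No split by arm is given anywhere; at 25% versus 35% with spread losses the type I error is only 5.5–6.4%.

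**The remedy.** A likelihood model looks unbiased under the assumptions above because dropouts are taken to resemble completers. It would not be protected if women leave for reasons tied to values never recorded.

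**A fuller plan.** A separate analysis plan may exist, so the absence of missing-data sensitivity analyses from an article is not counted here. The document also does not say whether values are carried by day or by week, so no fault is found on that.

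All of this stands, and it limits the size of the problem. It does not rescue the rule: the article itself fixes carrying forward for the primary analysis, and the bias under unequal dropout has no assured direction.

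**Conclusion.** The point holds as a weakness in the primary analysis that should be fixed, not as a demonstrated error in the sample size. With equal 30% dropout, the expected difference falls from 1.40 to about 1.1–1.2 if losses are spread over the visits, or to 0.98 if all come before week 4. Power is about 73–86% depending on timing, so a shortfall below 80% is possible but not established.

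The stronger reason to act is bias. With no true effect, type I error is about 7–11% for a 20% versus 40% split with spread losses (21% if baseline is carried for all), and about 5.5–9% for 25% versus 35% across all the timings examined. These figures rest on assumed timing, assumed splits and similar true change in dropouts and completers; the document supplies only the 30%, the falls and the SD.

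**What to change.** Replace the missing-data rule for the primary endpoint, before unblinding, with a likelihood-based repeated-measures model of the week 4, 8 and 12 diary means. Include arm, visit, arm-by-visit and baseline, with an unstructured covariance. Include all randomised women and take the arm contrast at week 12 as the primary result.

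The model is valid only if data are missing at random, so add a sensitivity analysis that lets dropouts do worse than the model predicts, including by different amounts in the two arms. Keep last value carried forward as a sensitivity analysis only.

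No new data are needed, since the three diaries are already scheduled. The cost is a change of wording, a little more analysis work, and a confidence interval that reflects the information actually missing.

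### The target is a proportional reduction (50% v 30%), but the primary test compares absolute changes without routine baseline adjustment, and no relative-scale analysis is fixed in advance

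*Protocol article*

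**What the plan says.** - **Target.** The Background section treats a reduction of at least 50% as the mark of a clinically relevant intervention. The section on statistical power and sample size sets the difference of interest at 20 percentage points. It starts from "With a baseline daily flush rate of 7.0 (SD 3.0") and takes "post-treatment flush rates of 3.5 and 4.9 for acupuncture and no acupuncture groups respectively", described as "equivalent to reductions of 50% and 30%, and SD 3.5 for change in flush rate".
- **Sizing.** The calculation works by "employing a two-sided, two-sample t-test for the changes", with the result that "100 women in each group were needed to identify a 20% difference with a power of 80" per cent. Allowing for 30% dropout, the total is 286.
- **Primary analysis.** Under data analysis and handling, it is intention-to-treat, "comparing mean changes from baseline to end of treatment after 12 weeks in the two groups, using a two-sample t-test". Analysis of covariance comes in only if baseline differences are judged meaningful.
- **Skew.** The same section says "It is anticipated that the data will be somewhat right-skewed, therefore analyses will be checked after appropriate data conversion", and the sentence goes on to add a non-parametric check. The conversion is not named.
- **Entry.** The abstract requires participants to document at least 7 flushes per 24 hours.

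**The concern.** The trial's question is framed as a ratio and its test as a difference. The two agree only at one baseline value: 20 percentage points equal 1.4 flushes a day when the mean baseline is 7.0, which is also the entry minimum. If recorded baselines respect that minimum and vary at all, their mean exceeds 7. The same 20 points is then a larger absolute difference, and under a proportional effect the SD of change rises too.

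A proportional effect also weights women unequally on the absolute scale. A fall from 20 to 10 counts 10/3.5 = 2.9 times as much as a fall from 7 to 3.5, although both are 50%.

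The planned checks do not close the gap. A rank test on absolute change keeps the absolute scale and gives no percentage. Covariance adjustment is conditional and also stays on that scale. A conversion may or may not yield a ratio, depending on which is chosen. At stake are some efficiency and a direct estimate, with its interval, of the quantity the protocol says it cares about.

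**Working it through.** **1. The plan's own figure.** Inputs from the sample size section: changes 7.0 − 3.5 = 3.5 and 7.0 − 4.9 = 2.1; difference 1.4; SD of change 3.5; two-sided 0.05; power 80%.

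n per group = 2 × (1.960 + 0.842)² × (3.5/1.4)² = 2 × 7.85 × 6.25 = 98.1, so 99. The exact t-test gives 99.08, so 100. Power at 100 per group is 80.4%. Total: 200/0.70 = 285.7, so 286. The stated figures reproduce, and sizing and primary test agree.

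**2. Percentage and absolute scales.** 20 points = 0.20 × mean baseline: 1.4 at 7, 2.0 at 10, 2.4 at 12, 2.6 at 13. Means above 7 are assumptions; the document gives none.

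**3. Power under a proportional effect with all baselines at least 7.** The document gives no SD on a ratio scale, so the distributions are assumed:
- 100 women per group, 800 runs per scenario.
- Baseline rate = 7 + a gamma excess (shape/mean 1/3, 1/3, 1/5, 0.6/6).
- Individual follow-up ratio gamma with mean 0.5 or 0.7 and the CV shown.
- Poisson counts over 14 baseline days and 7 days at week 12.
- Negative binomial model (NB) with log baseline and robust standard errors, dispersion held at its simulated value.

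| Scenario | Mean baseline | CV | Difference | SD of change (about) | Difference/SD | t-test on change | ANCOVA, raw counts | NB |
|---|---|---|---|---|---|---|---|---|
| A | 10 | 0.6 | 2.0 | 4.2 | 0.48 | 93% | 96% | 97% |
| B | 10 | 0.8 | 2.0 | 5.4 | 0.37 | 73% | 76% | 82% |
| C | 12 | 0.8 | 2.4 | 6.7 | 0.36 | 71% | 76% | 84% |
| D | 13 | 0.8 | 2.6 | 8.2 | 0.32 | 62% | 71% | 84% |

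The planned standardised difference is 1.4/3.5 = 0.40. The t-test falls below 80% where the SD of change grows faster than the difference (B to D).

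Gain of NB over the t-test: 4, 9, 13 and 22 points. Of this, baseline adjustment alone (ANCOVA minus t-test) gives 3, 3, 5 and 9; the change of scale gives 1, 6, 8 and 13. A second set of 1,000 runs gave t-test 92/76/74/64% and NB 97/84/85/85%, so gains of 5, 8, 11 and 21. With the dispersion estimated, as in practice, the range is 4 to 21 points.

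Under the null (ratio 0.6 in both arms), rejection rates were 5.0% for the t-test, 4.2% for ANCOVA and 4.8% for NB.

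**4. The rank check.** In the second set, Mann-Whitney on absolute change had 91/69/69/66% against 92/76/74/64% for the t-test: differences of −1, −7, −5 and +2 points. It does not recover the gain.

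**5. Other assumptions.**
- Baseline mean 7 and SD 3 with no floor, SD of change near 3.5, proportional effect: a t-test on log ratios against one on absolute change gave 94% v 78% (lognormal), 87% v 81% (gamma) and 83% v 76% (normal ratio).
- Other models with a floor of 7 and means of 10 or 12: the log-ratio test gained 0 to 5 points.
- Additive effect, near-normal data: the log-ratio test lost 7 points (68% v 75%). The baseline-adjusted NB model lost about 1 to 4 points.

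**6. Weight of heavy flushers.** Under a proportional effect, in the baseline distributions of step 5, the top quarter by baseline supplies about 35 to 40% of the absolute difference and the bottom quarter 11 to 19%, against 25% each under equal weight.

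**The case against.** The case for the plan is substantial, and most of it stands.

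- **Power.** A reader might infer that the trial lacks its stated 80%. The documents do not support that: the trial was sized for exactly this test, with a difference of 1.4 and an SD of 3.5, and the figure reproduces. Any loss is relative to another model. The scenarios with large gains have an SD of change of 5.4 to 8.2, and scenario D is heavily skewed, whereas the protocol expects only moderate skew.
- **Reading as a percentage.** A reader might infer that the result cannot be set against 50% v 30% at all. It can: the target is defined through group means, and mean change over mean baseline gives 3.5/7.0 = 50% and 2.1/7.0 = 30%. But the planned test and its interval are in flushes per day, so no interval for the relative effect follows directly.
- **Safeguards.** It would be wrong to say that the unnamed conversion is the only remedy. A non-parametric check is planned as well, and ANCOVA for baseline differences.
- **Skew.** Nothing shows the t-test to be invalid; it held its 5% level in the null run.
- **Influence.** To say that heavy flushers dominate is too strong for a 35 to 40% share.
- **Choice of model.** In scenarios A to D, a plain t-test on percentage change had 97/83/83/83% power, so the negative binomial model is one option among several.
- **Level of detail.** The name of a transformation may properly sit in an analysis plan that is not shown, so its absence alone is no finding. The primary test and its scale, however, are stated here, and they are what this point addresses.
- **Endpoint.** Flushes avoided per day is a legitimate clinical quantity and matches the stated endpoint. This is why the absolute comparison should stay primary.

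**Conclusion.** The point holds as a matter of efficiency and interpretation. The target is proportional, the confirmatory comparison is absolute and adjusted for baseline only on observed imbalance, and no stated check is sure to give a relative effect. The sample size and the validity of the t-test are not in question.

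If the effect is proportional and baselines start at 7, a baseline-adjusted ratio model gains about 4 to 21 points of power over the stated test, part of it from adjustment alone. Within those scenarios the small gain belongs to an SD of change of about 4.2 and the large one to about 8.2, against 3.5 planned. If the effect is additive, about 1 to 4 points are lost. All these figures rest on assumed distributions, because the document gives no variability on a relative scale. It is a worthwhile improvement of moderate weight.

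**What to change.** In the section on data analysis and handling:

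1. Keep the comparison of absolute change at 12 weeks as primary, and adjust it for baseline whether or not the arms differ.
2. Replace the unnamed conversion with one pre-specified supporting analysis on the relative scale that always includes baseline. An example is a log-link negative binomial model with robust standard errors for the week-12 diary count, with arm and log baseline rate as covariates and log days recorded as offset. It accommodates women who record no flushes.
3. Report the rate ratio with its confidence interval against the planned 0.50/0.70 = 0.71, beside the absolute difference in flushes per day.
4. State which analysis is primary and which is supporting, so that the two do not compete.

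The cost is a few lines of analysis text and a standard model; no extra participants or data are needed. The downside is that the ratio is model-based and slightly less efficient if the effect is additive.
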